### Data analysis

Descriptive statistics (ie, frequencies and percentages) will be used to report the demographic characteristics, primary outcome and secondary outcome by study group. Differences between study groups, with respect to the primary outcome, will be assessed using univariate and multivariate logistic regression, before and after adjusting for demographic covariates. As there are three study groups, pairwise comparisons will be performed to test for differences between any two groups. These analyses will be performed on an intention-to treat basis and per-protocol basis so that both the ‘real-world’ impact and the ‘potential’ impact of the interventions can be assessed (not all individuals will have a valid mobile number recorded on the GP clinical system and so not all intervention participants will be able to receive the text message reminder and PN interventions). To conduct the per-protocol analyses, we will include individuals with a mobile telephone number stored on the clinical system for the control group, individuals who successfully received a text message reminder for the text message reminder group, and individuals who answered the phone in the PN group. We will also perform subgroup analyses, to explore the effectiveness of the interventions, by demographic characteristics, on an intention-to-treat and per-protocol basis. Finally, we will perform a cost-effectiveness analysis, to estimate the costs of the interventions per additional person screened. This will involve dividing the total cost of intervention, by the number of additional people screened in each intervention arm, over and above the number screened in the control arm.

All analyses will be performed by using SSPS statistics (V.27.0).

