### Interventions

As described in Study design section, individuals will be randomised to receive either:

no intervention (‘usual care only’).A text-message reminder, 13 weeks after the invitation, with additional text-message reminders at 15, 17 and 19 weeks if there is no response (Individuals in the patient navigation group will receive a text message reminder at 13 weeks, in addition to patient navigation calls at 15, 17 and 19 weeks. This will allow iPlato (the company delivering the patient navigation telephone calls) to confirm which individuals’ telephone numbers are active, and call only those individuals who have an active telephone number. This will reduce the cost of the intervention, by ensuring only those with an active number are contacted (ie, less time spent attempting to contact individuals whose numbers are no longer valid/UpToDate)). (‘text message reminder(s)’).A text-message reminder, 13 weeks after the invitation, followed by PN calls at 15, 17 and 19 weeks if there is no response (‘text message reminder+PN telephone call(s)’).

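### The per-protocol sets follow a different rule in each arm, so both patient navigation contrasts for 'potential' impact lose the randomised comparison and can be biased in either direction

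*Protocol article*

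**What the plan says.** The Data analysis section of the protocol article plans the pairwise logistic regressions, and the subgroup analyses by demographic characteristics, on both an intention-to-treat and a per-protocol basis. The two are offered so that the real-world and the potential "impact of the interventions can be assessed". The reason given for the second analysis is that "not all individuals will have a valid mobile number recorded on the GP clinical system".

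The per-protocol sets are then fixed arm by arm:

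- Control: "individuals with a mobile telephone number stored on the clinical system for the control group".
- Text and PN: "individuals who successfully received a text message reminder for the text message reminder group, and individuals who answered the phone in the PN group".

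Three other places bear on this.

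- Blinding and randomisation: people are randomised at 13 weeks whether or not a mobile number is held.
- Study design and Interventions: both intervention arms get a text at week 13. PN calls follow at weeks 15, 17 and 19 only where there has been no response, and the provider will "call only those individuals who have an active telephone number".
- Data collection: the only participant characteristics extracted are sex, age and deprivation quintile. Adjustment is for demographic covariates.

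**The concern.** Two separate mechanisms break comparability in the PN contrasts.

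**Selection on behaviour.** People who answer a call may well differ from those who do not in how likely they are to return a kit. Non-answerers are removed from the PN set, but people who would not have answered cannot be identified in the control or text sets, so they stay there. Sex, age and deprivation are unlikely to capture this difference.

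**Successes removed by construction.** A PN-arm participant who counts as a responder before the first call at week 15 is not called, cannot have answered, and is excluded. The same person in the text arm received the same week-13 text and is kept. A control who returns a kit in that window is also kept, provided a number is stored. No assumption about behaviour is needed for this.

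The rule also goes beyond its stated reason. Missing or invalid numbers are a matter of availability, which the control rule addresses. Not answering is something else.

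At stake is the potential-impact estimate for PN, overall and by subgroup. PN against text is the comparison the Introduction says the trial is meant to make, and the Dissemination plan expects the results to inform whether the programme adopts either intervention.

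**Working it through.** **The plan's own figure.** The plan gives no figure for the per-protocol sets. Its sample size was reproduced to confirm the rates used below. With pooled variance, two-sided alpha 0.015 and 80% power, n = [z(0.9925)·√(2p̄(1−p̄)) + z(0.80)·√(p1(1−p1) + p2(1−p2))]² / (p2−p1)². For 0.0098 against 0.0318 this gives 901 per arm. The other two rows of Table 2 give 92 and 156. All three match.

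**Inputs.**

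- From Table 2: uptake p = 0.0318 (text) and 0.0098 (control).
- Assumed, because the documents give no values: c, the share of those called who answer; k, the kit-return rate of answerers divided by that of non-answerers; e, the share of eventual returners who count as responders before the first call.
- Simplification: everyone in the PN arm who has not responded is called, and everyone in the text arm receives the text.

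**PN versus text, with true uptake of 3.18% in both arms.** The odds ratio as randomised is 1.00.

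1. Remove early responders from the PN arm: r = p(1−e)/(1−pe).
2. Keep answerers only: a = k·r/(c·k + 1−c).
3. Compare with the text set, which stays at p: OR = [a/(1−a)] / [p/(1−p)], where p/(1−p) = 0.0318/0.9682 = 0.0328.

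Worked cases at c = 0.5:

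- e = 0, k = 2: a = 2 × 0.0318/1.5 = 0.0424; OR = (0.0424/0.9576)/0.0328 = 1.35.
- e = 0.25, k = 2: r = 0.02385/0.99205 = 0.0240; a = 0.0321; OR = 1.01.
- e = 0.25, k = 5: a = 5 × 0.0240/3 = 0.0401; OR = 1.27.
- e = 0.75, k = 1: a = r = 0.00795/0.97615 = 0.0081; OR = 0.25.

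All odds ratios at c = 0.5:

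| e | k = 1 | k = 2 | k = 3 | k = 5 |
|---|---|---|---|---|
| 0 | 1.00 | 1.35 | 1.53 | 1.70 |
| 0.25 | 0.75 | 1.01 | 1.14 | 1.27 |
| 0.50 | 0.50 | 0.67 | 0.76 | 0.84 |
| 0.75 | 0.25 | 0.33 | 0.38 | 0.42 |

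**PN versus control, with no effect of any intervention.** Put p = 0.0098, k = 3 and e = 0. For c = 30%, 50% and 70%, a = 0.0184, 0.0147 and 0.0123, and OR = 1.89, 1.51 and 1.25. With 901 controls and 901·c in the PN set, the chance of rejecting at two-sided 0.015 is 13.7%, 6.3% and 2.6%. This shows the upward mechanism alone; early returns would pull the other way, as in the table.

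**Under one baseline rule in all arms.** The arms remain exchangeable. With no effect, the expected odds ratio is 1.00 and rejection stays at the nominal level.

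**The case against.** The strongest reply is that this is a supporting analysis. Every comparison and subgroup is also run by intention-to-treat, the abstract does not mention per-protocol, and the label of potential impact signals a different question. That stands, and it limits the severity: randomisation, sample size and the intention-to-treat result are untouched.

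Four stronger readings are tempting, and the documents do not support them.

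- *Every arm uses a post-randomisation rule.* A stored number is an attribute of the record that allocation does not affect. Only text receipt and answering arise afterwards.
- *Anyone in the PN arm who returns a kit after the first text is never called.* Someone who returns a kit in week 16 may already have answered in week 15, and the article does not say what counts as a response. Only those counted as responders before week 15 certainly escape every call.
- *All three contrasts are equally damaged.* A stored number and a received text differ mainly by invalid numbers, and the text rule does not drop early successes. Control versus text is much less exposed.
- *The rule favours PN, by an odds ratio of about 1.35.* That figure leaves out early response. At the same inputs, early response by 25% of returners cancels it.

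It is also fair to say that equal uptake of 3.18% does not mean calls do nothing. The text arm can receive up to three further texts, so equality means that calls do as well as those texts. The table shows how far the per-protocol odds ratio moves from the randomised one. All of that movement is selection only if k reflects who answers and not what the call achieves.

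None of this restores comparability in the two PN contrasts.

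**Conclusion.** The point holds for PN versus control and PN versus text, in the per-protocol analyses and their subgroups. The rule is stated in the article, so this is not detail left to a later plan. The existence of the problem follows from the text alone. Its size does not, since the shares answering, responding early and returning kits are all assumed. In the PN-versus-text illustration at 50% answering, the odds ratio lies between about 0.25 and 1.27 when 25% to 75% of returners respond early, and is 1.35 with no early response and a twofold ratio, against a randomised value of 1.00. A reader might infer that the bias inflates PN or that the main result is compromised; the net direction cannot be settled from the document, and intention-to-treat is not affected. This should be fixed, but it is not a threat to the trial's main comparison.

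**What to change.** Define the second analysis set by one rule in all three arms: a mobile number on the GP system at randomisation. This is the rule already used for controls ("we will include individuals with a mobile telephone number stored on the clinical system for the control group"), with the time point added. Compare the arms as randomised within that set, including in the subgroup analyses. Report text-delivery and call-answer rates descriptively.

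A complier-average estimate could be added as an option. It should be limited to each intervention versus control, with the definition of receipt and the assumptions stated. Counting any delivered part of the intervention as receipt would not answer the question about people reached by phone, because a delivered week-13 text would qualify. PN versus text is less suitable, since both arms receive that text.

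Give the set a name distinct from intention-to-treat. The strengths and limitations box attaches that term to people with a recorded number, whereas Blinding and randomisation and Data analysis imply that everyone randomised is included. These passages need reconciling.

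The cost is mainly the wording of one paragraph. Number status at randomisation must be captured for all arms; it is not in the Data collection list, although the control rule already needs it. The downside is a more diluted estimate of potential impact, because people who held a number but were not reached stay in.

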#### Text message reminders

The text message reminders (SF 2, figure 2) for both intervention groups will remind recipients that they have not yet completed their kit, and that they are able to request a new one (should they wish to take part), via Freephone, from the BCSP. The following link, which provides relevant information in different patient languages, will be included in the text message reminder, to support individuals whose first language is not English: www.cancerchampionsgm.org.uk/wp-content/uploads/sites/2/2021/10/Bowel-Screening-%E2%80%93-Language-Support.pdf..

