#### PN telephone calls

The PN telephone calls will similarly remind recipients that they have not yet completed their kit and will provide them with the opportunity to request a new kit (should they wish to take part) via the London Bowel Cancer Screening Hub. In addition, the PN telephone calls will elicit barriers to participation, which the navigator will provide advice on, to support the individual in completing the test (see online supplemental appendix 2 for a copy of the PN script that will be used for this study). A record of all calls, and the barriers discussed, will be documented, to elucidate which barriers are successfully addressed by the PN calls (this will be confirmed by request and completion of a test kit).

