### Blinding and randomisation

This will be a single-blind RCT. The study investigators will not know which individuals have been assigned to the intervention or control groups, until the end of the trial, when all data have been collected and anonymised. Individuals registered at a participating GP practice will not be informed that they are participants in a study, during the study period; however, those receiving an intervention cannot be blinded to the condition they have been allocated, due to the overt nature of the interventions (hence, we describe this as a ‘single-blind’ RCT). Randomisation of individuals to study groups will be handled by iPlato, using simple, computerised, pseudorandom allocation methods. Individuals will be randomised in a 1:1:1 ratio to either the intervention or control condition, after 13 weeks of their screening episode, irrespective of whether or not they have a mobile number registered on their GP’s clinical system.

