### Data collection

At the end of the study (‘week 24’), the London Bowel Cancer Screening Hub will extract the following data on study participants, from the available bowel cancer screening system: sex, age, index of multiple deprivation quintile (derived from the participant’s postcode), adequate completion (ie, ‘kit returned’ (yes/no)) and bowel cancer screening result (normal/abnormal). The data will then be anonymised and analysed by a data analyst at the London Hub.

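### The cost-effectiveness denominator subtracts raw counts between arms that simple randomisation does not make equal; a difference in proportions is the sound form (minor, free to fix)

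*Protocol article*

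**What the plan says.** In the protocol article, the last part of the Data analysis section fixes a single cost-effectiveness measure: "This will involve dividing the total cost of intervention, by the number of additional people screened in each intervention arm". The additional people are those "over and above the number screened in the control arm". The subtraction is between numbers screened. Neither arm size nor a proportion enters the rule.

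The Blinding and randomisation section says: "Individuals will be randomised in a 1:1:1 ratio to either the intervention or control condition". The method is "using simple, computerised, pseudorandom allocation methods". No blocking or other restriction is described, so equal arms are the target but are not guaranteed.

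**The concern.** A difference of counts equals the number of extra people screened only if the two arms are the same size. If the text arm happens to be larger than the control arm, some of its surplus returns would have occurred without any intervention, simply because more people were in it. The rule credits those returns to the intervention and makes the cost per additional person look lower. If the text arm is the smaller one, the error goes the other way.

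This ratio is the only cost-effectiveness measure that the article describes. Cost-effectiveness is part of the stated aim, and the results are expected to bear on whether the programme adopts either intervention. The question is whether the error is large enough to matter.

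**Working it through.** **Inputs.** Table 2 (Sample size calculation): late uptake 0.0098 (control), 0.0318 (text) and 0.1334 (text plus PN); 901 per arm, 2703 in total. Blinding and randomisation: simple 1:1:1 allocation. The text above Table 2 gives 15.0% for PN. Table 2 is used here, and the higher figure would make the PN error smaller still.

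**1. The plan's own figure.** The documents give no cost-effectiveness figure, so the check starts from the sample size. The two-proportion formula with pooled variance under the null, two-sided alpha 0.015, 80% power and no continuity correction gives 901, 92 and 156 per arm for the three comparisons. All three match Table 2.

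**2. Expected additional people at equal arms.**
- Control: 901 x 0.0098 = 8.83
- Text: 901 x 0.0318 = 28.65, so 28.65 - 8.83 = 19.8 additional
- PN: 901 x 0.1334 = 120.19, so 120.19 - 8.83 = 111.4 additional

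**3. The gap between the two rules.** Let x be the number screened and n the number randomised, with k for the intervention arm and 0 for control.
- Count rule: x_k - x_0
- Proportion rule: n_k (x_k/n_k - x_0/n_0) = x_k - n_k x_0/n_0
- Count rule minus proportion rule: (n_k - n_0) x_0/n_0

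The error is therefore the arm-size difference times the observed control proportion.

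**4. How far arm sizes can differ.** Under simple randomisation of 2703 people to three equal arms, Var(n_k - n_0) = 2703 x 2/3 = 1802. The standard deviation is 42.4 and the 95% range is about -83 to +83.

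**5. Size of the error.** At the edge of that range, 83 x 0.0098 = 0.81 person.
- Text: 0.81/19.8 = 4.1%
- PN: 0.81/111.4 = 0.7%

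*Example.* Take 942 in the text arm and 859 in control, with returns at their expected values. The count rule gives 942 x 0.0318 - 859 x 0.0098 = 29.96 - 8.42 = 21.54. The proportion rule gives 942 x (0.0318 - 0.0098) = 20.72. The difference is 0.81 person.

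**6. Simulation.** In 400,000 simulated trials with random arm sizes and random returns at the Table 2 rates, the two rules had the same mean (19.8 text, 111.4 PN). Their difference within a trial had a 95% range of about -0.9 to +0.9 person, or about 4.5% of the text denominator and 0.8% of the PN denominator. This is slightly wider than step 5 because the observed control proportion also varies.

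**7. Against sampling error.** The standard deviation of the additional people screened is 6.1 in the text arm under either rule. In the PN arm it is 11.2 with counts and 11.1 with proportions. Arm-size imbalance adds almost nothing.

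**The case against.** The strongest reply is that the point is negligible. Allocation is 1:1:1, so the count rule has the correct expectation. The error is under one person at the edge of a 95% range, against a sampling standard deviation of 6.1 in the smaller of the two effects. No choice between the interventions would turn on it. The sentence may also be shorthand, since a condensed article need not spell out the estimator. All of this stands as regards size. It does not remove the point, because the article states a rule and that rule, read as written, is a difference of counts.

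A reader might go further and infer that the cost side is also wrong. The texts tell recipients that "they are able to request a new one (should they wish to take part), via Freephone, from the BCSP". The calls "will provide them with the opportunity to request a new kit (should they wish to take part) via the London Bowel Cancer Screening Hub". Yet the Hub's extract ends with "adequate completion (ie, ‘kit returned’ (yes/no)) and bowel cancer screening result (normal/abnormal" and has no field for kits sent. From this one might conclude that the plan understates cost. The documents do not support that:
- The numerator is the total cost of the intervention. It is not itemised, and kits are not excluded.
- The extract covers participant characteristics and outcomes. It lists no text or call costs either, so it is evidently not the only source of cost data.
- For PN the article says: "A record of all calls, and the barriers discussed, will be documented". The same section uses kit requests as confirmation that a barrier was overcome, so request data are foreseen there. No capture of Freephone requests is described, but that is silence and not contradiction.
- Cost components and their sources are commonly left to a fuller protocol or analysis plan.

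Nor do the documents show that order handling is costed in one arm and not the other. The PN arm receives the same Freephone text at 13 weeks, and requests made on calls also go through the Hub.

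**Conclusion.** The denominator point holds and is minor. The stated rule subtracts counts under an allocation method that does not guarantee equal arms. It is unbiased, but in a single trial it can be off by about 0.8 to 0.9 person: about 4% of the text denominator and under 1% of the PN denominator. These sizes assume the Table 2 rates and a total of 2703. The percentage for the text arm would be larger if the text effect proved smaller than planned.

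Two stronger conclusions should not be drawn. The rule does not systematically favour either intervention. The cost numerator is not shown to be in error. The documents give no kit price, no share of requested kits that are returned, and no share of late returns that use a replacement kit, so no percentage understatement can be computed from them.

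**What to change.** In the Data analysis section, define additional people screened as (proportion screened in the intervention arm minus proportion screened in the control arm) x number randomised to that intervention arm, and divide that arm's cost by the result. This is one sentence. It needs no new data or participants and leaves the expected value unchanged.

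Optional, and not a correction of an error: add the number of replacement kits sent to the Hub's extract for all three arms, and say whether kits count as intervention cost. That would be one extra field, and it would let kit costs be included if the sponsor decides that they belong in the ratio.

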Text message reminders, sometimes referred to as short messaging system reminders, are of particular interest to researchers seeking to reduce inequalities in screening, due to their relatively low cost, non-confrontational nature and the ubiquity of mobile telephones among the adult population (a recent survey by the Office for National Statistics indicated that over 95% of adults living in the UK own a mobile phone).^10^ A systematic review of text message reminders in cancer screening found them to be effective at improving participation rates by up to 15%, with the effectiveness of the reminder being contingent on a number of factors, including the content of the message and the number of messages sent.^11^

PN is another telephone-based intervention, one which involves the provision of personal support, from a trained ‘navigator’, to help patients overcome personal or system-related barriers to healthcare.^12^ As with text message reminders, PN is an intervention that has been of interest to researchers seeking to reduce inequalities in screening, due to the potential to deliver culturally tailored information to individuals whose main language is not English (eg, first-generation migrants). Previous studies have shown that such navigation can increase screening participation.^12^ Indeed, a review and meta-analysis conducted by Nelson *et al* showed a 64% increase in participation in colorectal, breast and cervical screening participation, with a PN intervention.^13^

While strong evidence indicates that both text message reminders and PN are effective, and the aggregate data indicate that PN results in larger effect sizes, few studies have directly compared the effectiveness and cost-effectiveness of these interventions with one another. As such, further research is needed to determine the most effective and cost-effective approach to promoting bowel cancer screening uptake and reducing inequalities in screening. The aim of this study, therefore, is to directly compare these two interventions so as to identify the most effective and cost-effective means to promote uptake of FIT screening in London.

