### Sample size calculation

For the control, text-message reminder and PN groups, we anticipate that 1.0%, 3.2% and 15.0% of participants (respectively) will complete a kit by week 24 (this is based on data provided by NHS England, as well as previous research conducted with the London BCSP) (Personal Communication). We subsequently designed our sample size calculation to provide sufficient power to allow us to test for the smallest possible difference, between any two groups, of 2.2 percentage points (ie, 1% in the control vs 3.2% in the text message reminder group). As three separate comparisons are planned for the main analysis (control vs text message reminders; control vs PN; text message reminders vs PN), we used an adjusted significance level (ie, 0.015) for our sample size calculation (as per the Bonferroni correction method, which takes into account inflation of the alpha statistic, caused by multiple comparisons), so as to maintain an overall 5% probability for any false positive result. To achieve 80% power at this level, our study requires 901 subjects per group (2703 recruits in total; see table 2 for details).

**Table 2 T2:** Sample size calculations

	P1	P2	Alpha*	Beta	n (per arm)	n (total)
Comparison 1						
No intervention† versusText-message reminders‡	0.0098	0.0318	0.015	0.2	901	2703
Comparison 2						
No intervention† versusText-message reminder+PN§	0.0098	0.1334	0.015	0.2	92	276
Comparison 3						
Text-message reminders versusText-message reminder+PN§	0.0318	0.1334	0.015	0.2	156	468

* An adjusted Alpha of 0.015 has been used to account for inflation of the statistic, resulting from multiple comparisons (ie, 0.05 / 3).

† Expected uptake based on 2019 data for FOBt/FIT, 13-24 weeks after invitation (PHE, personal communication).

‡ Expected uptake for text reminders based on the results of the service evaluation for the Southeast London breast screening service (iPlato, personal communication).

§ Expected uptake for text reminders and patient navigation based on the results of the service evaluation for the Southeast London breast screening service (iPlato, personal communication).

FITfaecal immunochemical test

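### The cost-effectiveness calculation compares each intervention with control only, so it does not give the patient navigation versus text ratio that the trial's aim calls for

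*Protocol article*

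**What the plan says.** The Introduction of the protocol article names the evidence gap: "few studies have directly compared the effectiveness and cost-effectiveness of these interventions with one another". It then sets the aim, which is to "directly compare these two interventions so as to identify the most effective and cost-effective means to promote uptake of FIT screening in London".

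For effectiveness, the plan follows that aim. The Sample size calculation section lists three comparisons ("control vs text message reminders; control vs PN; text message reminders vs PN"), and the Data analysis section plans pairwise tests between any two groups.

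For cost-effectiveness, the Data analysis section fixes one calculation. Its purpose is "to estimate the costs of the interventions per additional person screened". The method is stated in full: the numerator is the whole cost of delivering an arm, and this is divided "by the number of additional people screened in each intervention arm, over and above the number screened in the control arm". The article describes no ratio between the two intervention arms and gives no unit costs.

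**The concern.** The three arms are alternative policies. If text reminders are a live option, choosing between them and PN turns on what each further person screened costs when moving from text to PN. That is a difference in cost over a difference in uptake between those two arms. The planned ratios both start from no intervention, so neither answers the question.

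This is not a detail that a condensed article leaves to a fuller plan. The article states the calculation, and its comparator does not match the article's own aim. The Dissemination plan says that the results are likely to inform whether the programme uses PN, texts or both. A commissioner reading only the two planned ratios would see average cost per extra person over usual care. The price of the step from text to PN would not be shown, and it would not be settled in advance which ratio is the headline.

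A smaller point concerns the unit. The calculation subtracts numbers screened, while the Blinding and randomisation section specifies simple randomisation, which need not give equal arms.

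**Working it through.** **Inputs.** Expected uptakes from Table 2 are control pC = 0.0098, text pT = 0.0318 and PN pP = 0.1334. The running text gives 1.0%, 3.2% and 15.0%. Planned size is 901 per arm, 2703 in total. Costs are not in the article. Let cT and cP be the cost per person randomised in the text and PN arms, with no added cost in control. The ratio k = cP/cT is an assumption, varied from 2 to 100.

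**The plan's own figures.** No cost-effectiveness figure is stated. The uptakes are those behind the sample size: the pooled-variance formula for two proportions, two-sided alpha 0.015, power 80%, without continuity correction, gives 901, 92 and 156 per arm, exactly as in Table 2.

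**Extra people screened at 901 per arm.**
- Text over control: 901 × (0.0318 − 0.0098) = 19.8
- PN over control: 901 × (0.1334 − 0.0098) = 111.4
- PN over text: 901 × (0.1334 − 0.0318) = 91.5

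**Ratios.**
- Planned, text: cT / (pT − pC)
- Planned, PN: cP / (pP − pC)
- Not planned, PN versus text: (cP − cT) / (pP − pT)

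The third divided by the second is (1 − 1/k) × (pP − pC)/(pP − pT) = (1 − 1/k) × 0.1236/0.1016 = (1 − 1/k) × 1.217. It equals 1 when k = (pP − pC)/(pT − pC) = 0.1236/0.0220 = 5.62. As k grows, it approaches 1.217.

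With Table 2 uptakes and cT set to 1:

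| Assumed k | Text v control | PN v control | PN v text | PN v text ÷ PN v control |
|---|---|---|---|---|
| 2 | 45.45 | 16.18 | 9.84 | 0.608 |
| 3 | 45.45 | 24.27 | 19.69 | 0.811 |
| 5 | 45.45 | 40.45 | 39.37 | 0.973 |
| 5.62 | 45.45 | 45.45 | 45.45 | 1.000 |
| 10 | 45.45 | 80.91 | 88.58 | 1.095 |
| 20 | 45.45 | 161.81 | 187.01 | 1.156 |
| 100 | 45.45 | 809.06 | 974.41 | 1.204 |

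With 1.0%, 3.2% and 15.0%, the crossover is 0.140/0.022 = 6.36 and the limit is 0.140/0.118 = 1.186. At k = 10 the last column is 1.068, and at k = 20 it is 1.127.

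**Below the crossover.** PN screens more people and also has the lower cost per extra person versus control, so text is extendedly dominated. The relevant ratio is then PN versus control, which is already planned.

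**Raw counts.** With arm sizes nT and nC from simple randomisation of 2703, the variance of 0.0318·nT − 0.0098·nC is 2703 × [(0.0318² + 0.0098²) × 2/9 + 2 × 0.0318 × 0.0098 × 1/9] = 0.852, so the SD is 0.92 kits. That is 0.92/19.8 = 4.7% of the expected extra text returners. Binomial sampling alone gives an SD of √[901 × (0.0318 × 0.9682 + 0.0098 × 0.9902)] = 6.0 kits, about 30%.

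**The case against.** Control is a legitimate comparator. The Introduction says that neither intervention is currently implemented, so cost per additional person over usual care is the status-quo question. The versus-control ratios are incomplete for the head-to-head aim, but they are not wrong. This stands, and they should be kept.

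The planned output would not reverse the ranking. The cost ratio at which PN's planned ratio starts to understate the incremental one is also the ratio at which PN's planned figure rises above text's. Whenever there is an understatement, the planned figures already show PN as dearer per extra person. The missing ratio can also be derived by subtraction from the same arm costs and counts. Both points stand and limit the harm. They do not supply the number that a decision between the two needs, or fix it beforehand.

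A reader might infer that the calculation flatters PN. The documents do not support that as a general statement. They give no costs, and below a cost ratio of about 5.6 (6.4 at 15.0% uptake) the PN-versus-text figure is lower than PN's versus-control figure. A ratio above that is plausible for staffed calls against texts, but nothing in the article shows it.

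A reader might also say that the versus-control ratio credits PN with what the text arm would have achieved anyway. That treats PN as an addition to the full text arm. The Interventions section describes it otherwise: "A text-message reminder, 13 weeks after the invitation, followed by PN calls at 15, 17 and 19 weeks if there is no response". The PN arm gets one text and then calls, while the text arm gets up to four texts, so the text arm's uptake is not nested in the PN arm's.

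Finally, one sentence that speaks of numbers screened does not prove that unequal arms would be ignored. Interval methods for the ratio may fairly sit in a fuller plan, and their absence is no fault here.

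**Conclusion.** The point holds as a mismatch between a stated aim and a stated calculation. The aim is a direct comparison on cost-effectiveness, and the calculation yields two versus-control ratios and no PN-versus-text ratio.

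Its numerical size is conditional. At Table 2 uptakes, the incremental ratio exceeds PN's planned ratio only above a PN:text cost ratio of about 5.6, by about 10% at 10 times, 16% at 20 times and never more than 22%. At 15.0% PN uptake, the crossover is 6.4 and the ceiling 19%. Below the crossover, the planned PN ratio is the relevant one once text is ruled out by extended dominance. All of this assumes zero added cost in control and the design uptakes. A lower PN uptake would raise the ceiling and lower the crossover, but the article gives no such value, so no larger gap is claimed.

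The raw-count issue is minor: an SD of about 5% of the expected 20 extra text returners, small beside sampling error. The primary endpoint and its analysis are unaffected.

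**What to change.** Add to the Data analysis section the incremental ratio (cost PN − cost text) / (screened PN − screened text), with a check for simple and extended dominance that decides which ratio is read as the headline. If text is dominated, that is PN versus control. Otherwise, it is text versus control followed by PN versus text. Calculate all ratios by intention to treat, from cost per person randomised and proportion screened rather than raw counts. Keep the two versus-control ratios alongside.

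The cost is slightly more analysis. The arm costs and numbers screened are already needed for the planned ratios, and the numbers randomised are known from the trial, so nothing new is collected.
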